# Hypoglossal acupuncture for acute chemotherapy-induced dysgeusia in patients with breast cancer: study protocol of a randomized, sham-controlled trial

**DOI:** 10.1186/s13063-019-3525-y

**Published:** 2019-07-04

**Keywords:** Acupuncture, Cancer, Chemotherapy, Dysgeusia, Taste disorders, Randomized controlled trial

## Abstract

**Background:**

Distortion of taste sensations is a common chemotherapy-induced side effect; however, treatment evidence is limited. Pilot data indicated that acupuncture might be able to improve symptoms of dysgeusia. Thus, the aim of this study is to investigate the effects and side effects of hypoglossal acupuncture in the treatment of dysgeusia in patients with breast cancer undergoing chemotherapy.

**Methods/design:**

The study is a randomized controlled trial comparing a single verum acupuncture treatment with two active comparators: sham acupuncture and dietary recommendations. Sample size calculation revealed a total of 75 patients pending an alpha of 0.05, a power of 0.8, and an estimated effect size of 0.80. Patients with breast cancer undergoing platinum- or taxane-based chemotherapy will be included if they present with phantogeusia (abnormal taste sensations without an external oral stimulus) with an intensity of 4 points or above on an 11-point numeric rating scale (NRS). The primary outcome is phantogeusia; secondary outcomes include parageusia (abnormal taste of food), hypogeusia (reduced taste sensations), hypergeusia (increased taste sensations), xerostomia (dry mouth), stomatitis, appetite, and functional impairment. All outcomes will be assessed at baseline and prior to the next chemotherapy administration using an 11-point NRS for each. All adverse events will be recorded.

**Discussion:**

The results of this study will demonstrate the extent to which hypoglossal acupuncture may influence the intensity of and functional impairment due to chemotherapy-induced dysgeusia.

**Trial registration:**

Clinical Trials.gov, NCT02304913. Registered on 19 November 2014.

## Background

Taste disorders are frequent side effects in patients treated with chemotherapy [1, 2]. According to the National Cancer Institute Common Terminology Criteria for Adverse Events, dysgeusia is defined as a disorder characterized by abnormal or impaired sense of taste with mostly unpleasant metallic, bitter, or salty alteration of taste sensations [3]. Subconditions of dysgeusia include phantogeusia, an abnormal sensation of taste without presence of an external oral stimulus; parageusia, an abnormal taste of food; hypogeusia, a reduced sensation of taste; and hypergeusia, an increased sensation of taste. Although most forms of dysgeusia present persistent courses in quite a few cases, prevalence during chemotherapy ranged between 50% and 75% [1, 4], which is shown to significantly affect patients’ quality of life and may cause malnutrition, weight loss, and increased morbidity [3, 5, 6].

Cytostatic and cytotoxic chemotherapeutics mainly induce dysgeusia by destroying olfactory and taste receptor structures due to their inherently high turnover rates of 7 to 10 days. Several antineoplastic agents themselves also have metallic- or bitter-tasting contents that can reach taste receptors by diffusion through capillaries [1]. Direct sensitization or damage of neurons, moreover, can alter afferent taste pathways without the need for destroyed receptor cells or bad-tasting molecules from chemotherapeutic drugs [3]. Other chemotherapy side effects, such as oral mucositis, gastroesophageal reflux, or infections, and the intake of antibiotics or analgesics used to manage these side effects can exacerbate existing taste disturbances [2, 7].

Evidence for effective pharmacological treatment strategies of chemotherapy-induced dysgeusia is limited. Although current studies do not support the intake of amifostine [8, 9] or the substitution with zinc [10] or glutamine [11], dietetic counseling has provided the best available evidence to date and is recommended by several systematic reviews [1–3, 12] and the American Institute for Cancer Research. The effects of acupuncture for the treatment of dysgeusia have been examined in only one pilot trial in 37 patients with idiopathic dysgeusia, showing significant benefits of selected body and ear acupuncture points over sham acupuncture [13]. A literature search of standard medical databases revealed no randomized controlled acupuncture trials for dysgeusia in patients undergoing chemotherapy [14], but evidence was found for several other chemotherapy-related symptoms, such as nausea and vomiting and leukopenia, and a lower quality of evidence for pain, hot flashes, fatigue, and xerostomia [15–17]. Because in Traditional Chinese Medicine, taste disorders and functional disturbances of the tongue were particularly treated with needling of hypoglossal acupuncture points [18, 19], the aim of the present study is to investigate the effects of acupuncture under the tongue for acute chemotherapy-induced dysgeusia.

## Methods/design

### Objectives

The aim of this study is to examine the efficacy and safety of hypoglossal acupuncture in the treatment of acute dysgeusia in patients with breast cancer undergoing chemotherapy.

### Ethics

The trial protocol has been approved by the ethics committee of the Medical Faculty of the University of Duisburg-Essen, Germany (approval number 14–5953-BO), is registered with ClinicalTrials.gov (NCT02304913), and will be conducted in accordance with the ethical principles for clinical trials as defined by the Declaration of Helsinki. Before inclusion in the study, all patients have to provide written informed consent.

### Study design

The study is a randomized controlled clinical trial comparing verum acupuncture with two active comparators: sham acupuncture and standard medical care. It is designed according to the Standard Protocol Items: Recommendations for Interventional Trials (SPIRIT) 2013 statement [20], the Consolidated Standards of Reporting Trials (CONSORT) 2010 statement [21], and its Standards for Reporting Interventions in Clinical Trials of Acupuncture (STRICTA) 2010 extension [22]. If patients develop dysgeusia during chemotherapy and meet the eligibility criteria of this study, baseline data will be assessed at the individual’s next chemotherapy appointment, directly before chemotherapy administration (T_0_). Afterward, patients will be randomized 1:1:1 to one of the three groups. Patients of the acupuncture groups will receive either verum or sham acupuncture; patients of the standard medical care group will receive written, evidence-based dietary recommendations. Outcomes will be reassessed just before the next chemotherapy administration (T_2_) as well as between the chemotherapy administrations using a daily patient log (T_1–2_) (Figs. 1 and 2). Patient recruitment started in January 2015. Estimated primary completion date is December 2019.

**Fig. 1 Fig1:**
[figure not shown]
CONSORT flow chart

**Fig. 2 Fig2:**
[figure not shown]
SPIRIT figure

### Randomization

A researcher who was not involved in conducting the study generated a stratified (by age and type of chemotherapy because both variables are found to affect the course of dysgeusia [23, 24]) random allocation sequence with randomly varying block lengths using Random Allocation Software [25]. The randomization list is password-secured, and no person other than the aforementioned researcher is able to access it. On the basis of this list, the researcher prepared sealed and opaque envelopes sorted in ascending order of randomization. Allocation to the groups will be executed by the study physician, who is involved in neither the random sequence generation nor the assessment of study outcomes.

### Blinding

First, patients of the two acupuncture groups will be blinded to whether they receive verum or sham acupuncture. Second, the outcome assessors delivering questionnaires to patients will remain blind to patients’ group allocations during the whole study period. Third, the statistician will be blinded to group allocation during data analysis by renaming groups with numbers.

### Participants

Patients will be recruited from the Department of Gynecology & Gynecologic Oncology, Kliniken Essen-Mitte, Germany. Interested patients with symptoms of phantogeusia are screened by the attending physician and receive detailed written study information and have an enrollment visit with the study physician on the day of their next chemotherapy administration. For inclusion in the study, all eligibility criteria have to be met and written informed consent must be obtained from the patient prior to inclusion.

Inclusion criteria are as follows:Patients with breast cancer (TNM stages I–III) undergoing initial treatment with platinum- or taxane-based chemotherapy (regardless of the length of the chemotherapy cycle)Phantogeusia intensity of 4 points or above on average on an 11-point numeric rating scale (NRS) since the last chemotherapy administrationWillingness to participate in the study and provision of written informed consent

Exclusion criteria are as follows:Severe stomatitisDysgeusia before chemotherapy (based on neurological diseases, diabetes, or ingestion of drugs with taste disorders as a side effect)Leukopenia/neutropeniaTreatment with anticoagulants and/or hemophiliaSmokerSevere physical or mental comorbidity (whereby the patient is unable to participate in the study)Use of other complementary treatments that might influence patients’ tasteParticipation in other studies of interventions for oral complications due to chemotherapy

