### Interventions

#### Verum acupuncture group

Patients of the verum group receive a single treatment of hypoglossal needle acupuncture during their next chemotherapy administration after study inclusion. Treated acupuncture points will be Jinjin (Golden Liquid/EX-HN12) left beside the lingual frenulum and Yuye (Jade Fluid/EX-HN13) right beside the lingual frenulum. Both points are treated in quick succession with immediate removal of the needle (Table 1).

**Table 1 Tab1:** Details of the acupuncture treatment according to STRICTA

STRICTA items		Detailed protocol description
Acupuncture rationale	(a) Style of acupuncture	Traditional Chinese needle acupuncture
	(b) Reasoning for treatment provided	Selected traditional acupuncture points for dysfunction of the tongue
	(c) Extent to which treatment was varied	Acupuncture with immediate removal of the needle
Details of needling	(a) Number of needle insertions	Two needle insertions per subject
	(b) Names of points used	Jinjin (Ex-HN 12), Yuye (Ex-HN13)
	(c) Depth of insertion	1–2 mm
	(d) Response sought	No De-Qi sensation
	(e) Needle stimulation	No stimulation
	(f) Needle retention time	2–3 s for each acupuncture point
	(g) Needle type	TeWa CB-Type 2540 (0,25 × 40 mm), medical stainless steel with copper handle (asia-med GmbH & Co. KG, Germany)
Treatment regimen	(a) Number of treatment sessions	Single treatment session
	(b) Frequency and duration of treatment sessions	During the received chemotherapy administration
Other components of treatment	(a) Details of concurrent interventions	No concurrent interventions
	(b) Setting and context of treatment	Outpatient clinic, all treatments in a specific study center will be performed by the same practitioner
Practitioner background	(a) Description of participating acupuncturists	Licensed Traditional Chinese Medicine practitioner with 5 years of studies at the Tianjin University (China) and 3 years of acupuncture treatment experience in a clinical oncological setting
Control or comparator interventions	(a) Rationale for the control or comparator	Non-penetrating sham acupuncture
	(b) Precise description of the control or comparator	Sham points: 1 to 1.5 cun (1 to 1.5 thumb’s width) beside the verum acupuncture points using the dull side of the needle

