### Primary outcome

The primary outcome is phantogeusia [11, 29, 30], a continuous abnormal taste sensation without an external oral stimulus, as assessed at follow-up (T_2_) by an 11-point NRS.

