### Statistical analysis

Data will be analyzed using IBM SPSS Statistics for Windows software, release 22.0 (IBM Corp., Armonk, NY, USA). Patients’ characteristics will be presented separately for each group using descriptive statistics, including mean and standard deviation, median and range, frequencies and proportions, based on the data format and distribution.

Data analysis will be conducted according to the intention-to-treat principle; that is, all randomized patients regardless of compliance or withdrawal will be included. Missing values will be multiply imputed by the Markov chain Monte Carlo method [37, 38], yielding a total of 50 complete datasets. Statistical tests will be conducted in a hierarchical order, starting with the comparison of acupuncture vs. usual care, which in case of significant effects will be followed by the comparison of acupuncture vs. sham acupuncture.

The primary outcome will be analyzed as a function of the treatment group (verum acupuncture versus standard medical care), patients’ expectations, and their respective baseline values (linear covariates) using a univariate analysis of covariance. Between-group differences and 95% confidence intervals were estimated using two-sided *t* tests and an alpha level of 5%. If the analysis reveals a statistically significant between-group difference, a second univariate analysis of covariance on the primary outcome will be conducted as a function of the treatment group (verum acupuncture versus sham acupuncture), patients’ expectations, and their respective baseline values (linear covariates). Between-group differences and 95% confidence intervals were estimated using two-sided *t* tests and an alpha level of again 5%. Because of hierarchical testing of the hypotheses, no alpha level adjustment is necessary [39]. The same covariance models will be applied for secondary outcome measures; for those effect measures, confidence intervals and *P* values will be reported descriptively. Moreover, a Kaplan-Meier survival analysis will be used to analyze group differences regarding the time point of symptom relief based on the daily patient log. Data on tolerability and safety will be reported descriptively. No interim analysis will be conducted.

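### The interval from treatment to the primary rating varies with cycle length, yet the stated ANCOVA omits cycle length and the randomization strata, which leaves avoidable variance in the primary analysis

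*Protocol article*

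**What the plan says.** Under Participants, the protocol article accepts breast cancer patients on platinum- or taxane-based chemotherapy "regardless of the length of the chemotherapy cycle".

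Under Study design, T0 is tied to an administration: "baseline data will be assessed at the individual’s next chemotherapy appointment, directly before chemotherapy administration". Treatment falls at that same administration; the verum arm will "receive a single treatment of hypoglossal needle acupuncture during their next chemotherapy administration after study inclusion". For follow-up the section says "Outcomes will be reassessed just before the next chemotherapy administration", and gives no day or window. The primary outcome is phantogeusia "as assessed at follow-up (T_2_) by an 11-point NRS".

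Under Randomization, the list is stratified by age and type of chemotherapy, on the ground that both influence how dysgeusia develops. How the strata are cut is not described.

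Under Statistical analysis, the primary model has treatment group plus "patients’ expectations, and their respective baseline values (linear covariates) using a univariate analysis of covariance". Verum is first compared with standard care and then, if that is significant, with sham. Secondary outcomes use the same models. A daily log between T1 and T2 feeds secondary outcomes and a Kaplan-Meier analysis of time to relief.

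**The concern.** Baseline and treatment share one administration and the primary rating comes just before the next, so the treatment-to-outcome interval equals one cycle. The inclusion criterion expressly lets that length vary. If the phantogeusia score depends on time since chemotherapy, the primary analysis pools ratings taken at different points of the time course. The Kaplan-Meier analysis shows that the authors expect symptoms to ease at some point between visits, so such dependence is plausible.

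The model then ignores what is known about this variation. Planned cycle length is known at randomization and is not a covariate. Age and type of chemotherapy were thought important enough to stratify on, and they are not covariates either. What is at stake is precision in a trial of 25 per arm. The sham comparison is tested only if the first comparison succeeds, so a loss of power there also affects the second test.

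**Working it through.** **1. The plan's own figure.** Inputs from Sample size calculation: d = 0.8, two-sided α = 0.05, power 0.8, t test, 25 per group. The normal approximation gives 25 per group (power 0.807). The noncentral t distribution gives power 0.791 at 25 per group and needs 26 for 0.80. The stated figure reproduces; there is no arithmetic error here.

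**2. Assumed inputs.** The article gives none of these:
- within-cycle SD of the rating: 2 NRS points, so d = 0.8 is a raw difference of 0.8 × 2 = 1.6
- half the patients on short cycles and half on long cycles
- mean difference between short and long cycles, δ: 2 or 3 points
- within-cycle correlation of T0 and T2 scores, ρ: 0.3, 0.5 or 0.7

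**3. The same gap sits in the baseline score.** T0 is taken at the end of the patient's preceding cycle and T2 at the end of the following one. If the schedule does not change, δ is present at both times. Then, within an arm:
- Var(T0) = Var(T2) = V = 4 + δ²/4
- Cov(T0, T2) = C = 4ρ + δ²/4
- residual variance, ANCOVA without cycle length = V − C²/V
- residual variance with cycle length added = 4(1 − ρ²)

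Example, δ = 2 and ρ = 0.5: V = 5 and C = 3, so the residual variance is 5 − 9/5 = 3.2, against 4 × 0.75 = 3.0 with cycle length.

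**4. Power.** Noncentrality = (1.6/√residual variance) × √(25/2). Degrees of freedom are 50 − 4 = 46 for the stated model (intercept, group, expectations, baseline) and 45 with cycle length. Expectations are given no explanatory value.

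| ρ | δ | Residual variance, stated model | Residual variance, with cycle length | Power, stated | Power, with cycle length | Loss (points) |
|---|---|---|---|---|---|---|
| 0.3 | 2 | 4.03 | 3.64 | 0.788 | 0.827 | 3.9 |
| 0.3 | 3 | 4.35 | 3.64 | 0.757 | 0.827 | 7.0 |
| 0.5 | 2 | 3.20 | 3.00 | 0.872 | 0.892 | 2.0 |
| 0.5 | 3 | 3.36 | 3.00 | 0.856 | 0.892 | 3.6 |
| 0.7 | 2 | 2.11 | 2.04 | 0.968 | 0.972 | 0.4 |
| 0.7 | 3 | 2.17 | 2.04 | 0.964 | 0.972 | 0.8 |

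**5. Price of the extra terms if they explain nothing.** At ρ = 0.5 and residual variance 3.0, power is 0.8920 on 46 degrees of freedom, 0.8917 on 45 and 0.8907 on 42. Four useless covariate terms cost about 0.1 power point.

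**The case against.** The strongest objection is that admitting any cycle length is an open, pragmatic choice, that randomization balances cycle length between arms in expectation, and that the baseline covariate already carries most of a stable cycle-length difference. All of this stands. It removes any claim of bias and keeps the loss small. It does not justify leaving a known prognostic variable, and the trial's own strata, out of a fully listed model.

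It can also be said that d = 0.8 is standardized and may already refer to the SD of a mixed population. That is fair, since the article gives no raw difference or SD. The table therefore shows what adjustment could gain, and not that the sample size is wrong.

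A reader might infer more than the document supports:
- **A power loss of 9 to 19 points.** An unadjusted t test with the same inputs gives d = 1.6/√5 = 0.716 and power 0.70 for a 2-point gap, and d = 1.6/2.5 = 0.64 and power 0.60 for 3 points. The plan is an ANCOVA on baseline, so this is the wrong analysis.
- **Power of 28%.** This needs d = 0.4, that is, no effect at all in the long-cycle half. Nothing in the article suggests that.
- **Floor effects or a change of recall between entry and T2.** The Primary outcome section says when the scale is given, not what period it covers. A condensed article need not print the item.
- **Natural recovery within a cycle, from "inherently high turnover rates of 7 to 10 days".** The Background offers this as a reason why taste structures are vulnerable, not as a recovery time. It also describes persistent courses and nerve damage.
- **Patients in their last cycle have no T2.** The article is silent, and the full protocol may provide for them.

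**Conclusion.** The point holds as one of precision. The treatment-to-outcome interval varies by design, and the stated ANCOVA omits cycle length and both stratification factors. The arm comparison is not biased. Under the assumptions above, omitting cycle length costs from under 1 to about 7 power points, and about 2 to 4 at a baseline correlation of 0.5.

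These figures rest on the assumed SD, regimen mix, gap and correlation, and on cycle length staying the same before and after T0. If a patient's schedule changes at that point, baseline absorbs less and the loss is larger; the article does not show how often that happens. The possible gain from the strata was not quantified, because the article gives nothing to base it on.

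**What to change.** 1. Add planned cycle length (short versus long, fixed at randomization) and the randomization strata (age, type of chemotherapy) as covariates in the primary and secondary ANCOVAs. This costs a few degrees of freedom and some analysis-plan wording. It recovers precision but does not equalize the timing of T2.
2. To address timing, add a supporting analysis that compares arms on mean daily-log phantogeusia over one early window common to all patients, no longer than the shortest cycle admitted. The data are already collected.
3. If the full protocol does not already provide for it, state that where no next administration takes place the T2 questionnaire is collected on the date it would have been due, and is not imputed. This would mean a few questionnaires by post or telephone, with no added visits or patients.

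The article reports recruitment as ongoing and plans no interim analysis, so the changes should be fixed before allocation is revealed to the statistician.

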### Interventions

#### Verum acupuncture group

Patients of the verum group receive a single treatment of hypoglossal needle acupuncture during their next chemotherapy administration after study inclusion. Treated acupuncture points will be Jinjin (Golden Liquid/EX-HN12) left beside the lingual frenulum and Yuye (Jade Fluid/EX-HN13) right beside the lingual frenulum. Both points are treated in quick succession with immediate removal of the needle (Table 1).

**Table 1 Tab1:** Details of the acupuncture treatment according to STRICTA

STRICTA items		Detailed protocol description
Acupuncture rationale	(a) Style of acupuncture	Traditional Chinese needle acupuncture
	(b) Reasoning for treatment provided	Selected traditional acupuncture points for dysfunction of the tongue
	(c) Extent to which treatment was varied	Acupuncture with immediate removal of the needle
Details of needling	(a) Number of needle insertions	Two needle insertions per subject
	(b) Names of points used	Jinjin (Ex-HN 12), Yuye (Ex-HN13)
	(c) Depth of insertion	1–2 mm
	(d) Response sought	No De-Qi sensation
	(e) Needle stimulation	No stimulation
	(f) Needle retention time	2–3 s for each acupuncture point
	(g) Needle type	TeWa CB-Type 2540 (0,25 × 40 mm), medical stainless steel with copper handle (asia-med GmbH & Co. KG, Germany)
Treatment regimen	(a) Number of treatment sessions	Single treatment session
	(b) Frequency and duration of treatment sessions	During the received chemotherapy administration
Other components of treatment	(a) Details of concurrent interventions	No concurrent interventions
	(b) Setting and context of treatment	Outpatient clinic, all treatments in a specific study center will be performed by the same practitioner
Practitioner background	(a) Description of participating acupuncturists	Licensed Traditional Chinese Medicine practitioner with 5 years of studies at the Tianjin University (China) and 3 years of acupuncture treatment experience in a clinical oncological setting
Control or comparator interventions	(a) Rationale for the control or comparator	Non-penetrating sham acupuncture
	(b) Precise description of the control or comparator	Sham points: 1 to 1.5 cun (1 to 1.5 thumb’s width) beside the verum acupuncture points using the dull side of the needle

